### Analyses and statistics

This is a series of three experiments in a double-blind, placebo-controlled, randomized, cross-over design. Exp. I: LTG vs. placebo on group 1, Exp. II: LOV vs. placebo on group 1, Exp. III: LTG vs. placebo on group 2.

Sample size: Sample size calculation was done using the primary endpoints, nQuery Advisor, and expected means of MEP amplitudes and standard deviation (SD) for the different measurements from Mainberger et al. [7].

**Table Taba:** 

	Timepoint 1 (T1)	Timepoint 2 (T2)	Timepoint 3 (T3)
**Lovastatin LTP (increase in mean MEP) data (Mainberger et al. **[7]**) with common SD of 0.5**			
Healthy controls	1.440	1.600	1.710
NF1	0.920	0.970	0.980
Difference	0.520	0.630	0.730
**Experiments I and II**			
Local α	0.025	0.013	0.008
Power with 14 patients	89%	95%	97%
Power with 12 patients	82%	89%	94%
**Experiment III**			
Local α	0.050	0.025	0.017
Power with 14 patients	94%	97%	99%
Power with 12 patients	90%	94%	97%

An increase in MEP amplitudes over time is considered to refer to the concept of long-term potentiation (LTP)-like plasticity as it has been demonstrated in Mainberger et al. [7] as well. Twelve patients per disease entity will be enough to provide appropriate power to all planned primary endpoint tests (two-sided paired samples *t*-tests) with a global significance level of 5% and adjusted local significance levels using the Bonferroni-Holm procedure. In order to account for some unobtainable data and drop outs, the sample size will be increased to 14 patients per disease (28 trial participants in total).

Analysis sets: For each experiment, there will be a separate analysis set defined, as it is possible that a patient is suitable for analysis in only one of the first two experiments. All analyses will be performed on the full analysis set (FAS-I, FAS-II, FAS-III), consisting of all patients who delivered a full set of MEP measurements within the corresponding experiment. Since all measurements will take place within a very short time per patient, it is expected that the data will be either complete or entirely missing.

Primary endpoint: The primary endpoint analyses will be performed in three separate testing procedures. The global significance level will be 5%. Since experiments I and II are done on the same set of patients, the significance level for those two experiments will each be 2.5%. The significance level of experiment III will be 5%. The primary endpoint analysis will consist of three series of three paired samples two-sided* t*-tests, comparing MEP under verum vs. placebo at the three measurement time points. The local significance level will be adjusted using the Bonferroni-Holm procedure and will be as follows for the ordered by *p*-value tests:

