#### Experiment III—Lamotrigine (LTG) in patients with NF1

Participants receive 300 mg single dose LTG or placebo 2 h before TMS [11]. After at least 7 (up to 60) days, a cross-over takes place: participants receive placebo or 300 mg single dose LTG 2 h before TMS (Table 2, Additional file 1).

**Table 2 Tab2:** Schedule of procedures and visits patient group 2, NF1

*Study overview medication*	**Baseline visit (or day 1)**	**Visit 1 (day1)** **D1**	**Visit 2 (7–60 days after V 1)** **D8–61**
		Exp. III: Lamotrigin (LTG) or Placebo	
Informed consent	**X**		
Eligibility criteria	**X**		
Demographics	**X**		
Medical/surgical history	**X**		
Vital signs	**X**	**X**	
Pregnancy test^a^	**X**	**X**	
Randomization		**X**	
Exp. III: LTG or PLC) Single dose		**X**	**X** **(cross-over)**
TMS (EMG integrated)^a^		**X**	**X**
TAP		**X**	**X**
Concomitant medication	**X**	**X**	**X**
AE/SAE		**X**	**X**

^a^To be performed after having obtained informed consent; if baseline is less than 5 days prior to V1, a second pregnancy test is not necessary

^b^TMS to be performed 2 h after intake of LTG

Experiments I and II take place with a sufficient time gap on the same set of patients (Fig. 1). It is not possible to conceal treatment in a triple cross-over design in group 1, which is why two separate tests have been planned on group 1.

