### Endpoints and endpoint rationale

The *primary endpoint* for each experiment is the difference between the amplitude of the motor evoked potential (MEP) elicited with transcranial magnetic stimulation (TMS, measured at three time points after interventional TMS for each investigation) after placebo and after medication (LTG and LOV).

Changes in MEP are a well-established and safe method to probe changes in cortico-spinal excitability in humans [18]. MEPs are elicited by TMS using a figure-of-eight coil with an outer diameter of 100 mm centred tangentially on the scalp over the primary motor cortex (M1) of the nondominant hand with its handle pointing in a posterior direction and laterally at an angle of approximately 45° away from the midline. MEPs are recorded from the abductor pollicis brevis (APB) muscle at rest by surface electromyography (EMG) using silver/silver chloride electrodes with a surface area of 263 mm^2^ (AMBU, Ballerup, Denmark) mounted in belly-tendon recording technique. Data are band-pass filtered (20–2000 Hz) and amplified using an Ekida DC universal amplifier (EKIDA GmbH, Helmstadt, Germany), digitized at 5 kHz sampling rate using a MICRO1401*mkII* data acquisition unit (Cambridge Electronic Design Ltd, Cambridge, UK) and stored on a standard personal computer for online visual display and later offline analysis using Signal Software version 5 (CED Ltd, UK). MEP size is determined by measuring the two highest peaks of opposite polarity. Twenty trials will be recorded and then averaged for each point of investigation as described elsewhere [15, 16]. Resting motor threshold is recorded to probe changes in local cortical excitability [19].

The *secondary endpoints* for each experiment include the difference between the neuropsychological testing of attention by the TAP and differences in short interval cortical inhibition (SICI) after placebo and after medication (LTG and LOV) [6, 20]. Another endpoint is the comparison of LTG and LOV effects on synaptic plasticity and attentional performance in the NS group. The TAP is a well-established tool and used to measure the influence of LTG and LOV on attention [7, 20]. We previously demonstrated that LOV leads to an amelioration of attentional performance in humans with NF1 [6]. Consequently, we hypothesized that this would also lead to better attention in patients with NS and that LTG ameliorates attention in NF1 and NS.

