For SICI, a subthreshold conditioning stimulation is delivered 2, 3 and 5 ms before a test stimulus [6]. It has been demonstrated before that an increased inhibition is the most prominent factor in mice with NF1 to prevent synaptic plasticity [5]. The authors have previously demonstrated that LTG is a potent modulator of synaptic plasticity in healthy humans [10]. Decreasing intracortical inhibition by LOV was associated with an increase in synaptic plasticity in patients with NF1 [6]. The central role of intracortical inhibition regulating synaptic plasticity in NF1 has recently been certified by animal studies revealing a new option of pharmacological intervention with LTG [5]. We have previously shown that LOV leads to a disinhibition in patients with NF1 and, therefore, hypothesized that this would be a key factor to normalize cortico-spinal excitability in patients with NF1 and NS.

*Safety measures* include documentation of blood pressure and heart frequency prior to the intervention as well as monitoring of EMG activity during TMS intervention and documentation of adverse events (AE), severe adverse events (SAE) and suspected unexpected serious adverse reactions (SUSAR) following established definitions and legal requirements. The intensity of AEs is defined according to the common terminology criteria for adverse events (CTCAE Version 4.0, https://www.eortc.be/services/doc/ctc/CTCAE_4.03_2010-06-14_QuickReference_5x7.pdf).

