**Table Tabb:** 

Experiment	Test number	Local significance level
I and II	1	0.025
I and II	2	0.013
I and II	3	0.008
III	1	0.050
III	2	0.025
III	3	0.017

Secondary endpoints and safety: Analyses of baseline and safety data and secondary endpoints will be done using appropriate descriptive statistics and paired sample tests for difference between the two study groups. All tests will be two-sided with an exploratory significance level of 5%. No adjustment for multiple comparisons will be done.

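### The full-MEP completer rule governs every analysis, so a dosed patient without a full MEP set drops out of that experiment's planned safety, TAP and SICI analyses

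*Protocol article*

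**What the plan says.** All points are from the protocol article.

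- **Scope of the set** (Analyses and statistics, Analysis sets): "All analyses will be performed on the full analysis set (FAS-I, FAS-II, FAS-III"). No exception is made for safety or secondary endpoints.
- **Membership** (same paragraph): each set is defined as "consisting of all patients who delivered a full set of MEP measurements within the corresponding experiment". The sets are separate because "it is possible that a patient is suitable for analysis in only one of the first two experiments".
- **Reason given** (same paragraph): "Since all measurements will take place within a very short time per patient", data are expected to be all present or all absent for a patient.
- **Safety and secondary analyses** (Secondary endpoints and safety): "Analyses of baseline and safety data and secondary endpoints will be done using appropriate descriptive statistics", together with paired tests. No population is named.
- **Secondary endpoints** (Endpoints and endpoint rationale): these include "the difference between the neuropsychological testing of attention by the TAP" and SICI, each compared between placebo and active drug.
- **Safety measures** (same section): these include "documentation of adverse events (AE), severe adverse events (SAE) and suspected unexpected serious adverse reactions (SUSAR").
- **Spacing of sessions** (Experiment III): "After at least 7 (up to 60) days, a cross-over takes place". Experiment I has the same interval.

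**The concern.** The set carries the name of a full analysis set but works as a completer set. The primary test pairs active drug with placebo at three time points, so a full set of MEPs means both sessions with every block. An efficacy measurement thus decides who is counted for safety and for attention.

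In a cross-over, the most natural partial dropout is one period done and the other missing. A patient who takes the active drug in period 1, feels unwell and does not come back would be removed from that experiment's safety summary because the second session is missing. Exclusion can then depend on the outcome being summarised. This matters because the Risk/benefit analysis says both drugs are used off-label and above the labelled dosage, and because the Conclusion expects the results to help design larger trials.

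For TAP and SICI the loss is simpler: usable paired data are discarded because a different measurement failed.

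**Working it through.** **1. The plan's own figures.** The only related calculation is the power table, which carries the dropout allowance. Inputs: differences 0.520, 0.630 and 0.730; SD 0.5, taken as the SD of the paired difference; two-sided paired t-test; noncentrality = difference / 0.5 × √n on n − 1 degrees of freedom. Local levels are 0.025, 0.0125 and 0.00833 for Experiments I and II, and 0.05, 0.025 and 0.0167 for Experiment III.

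| Experiment | n | Stated power (T1/T2/T3) | Recomputed |
|---|---|---|---|
| I and II | 14 | 89/95/97% | 89.6/94.8/98.0% |
| I and II | 12 | 82/89/94% | 82.6/89.0/94.3% |
| III | 14 | 94/97/99% | 94.9/97.7/99.2% |
| III | 12 | 90/94/97% | 90.6/94.5/97.5% |

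The stated values reproduce to about one percentage point. They concern the primary test only, so a separate safety set does not alter them.

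**2. Does the schedule support the reason given?** Set membership is judged within one experiment, so the relevant interval is the one between that experiment's two TMS sessions.

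- Experiments I and III: 7 to 60 days.
- Experiment II, from Table 1: TMS at Visits 4 and 6. Visit 5 is 14 to 60 days after Visit 4, and Visit 6 is 3 days after Visit 5, which gives 14 + 3 = 17 to 60 + 3 = 63 days. (The Fig. 1 caption gives a 7-day minimum pause for Experiment II where the text and Table 1 give 14. Those places need reconciling, but the argument holds under either.)

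Within a session the MEPs are taken over about an hour, so the reasoning is plausible there. It does not carry over to two sessions at least a week apart. The plan also allows for unobtainable data and dropouts when it raises the sample from 12 to 14 per disease.

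**3. Who is lost under the rule as written?**

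- Dosed in period 1, no second session: outside that experiment's set, so outside its safety analysis.
- TAP or SICI measured under both treatments, one MEP block missing: outside the TAP and SICI analyses.
- Completes Experiment I, drops out of Experiment II: stays in FAS-I, is outside FAS-II.
- Leaves after the last MEP: stays in.

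**4. Size.** The document gives no count. Assumption: of the allowance 14 − 12 = 2 (2/14 = 14.3%), k = 0, 1 or 2 were dosed. To bound the effect, assume that each of these k patients left because of an adverse event and that nobody else had one. Intervals are exact (Clopper-Pearson) and two-sided. For zero events in n the upper limit is 1 − 0.025^(1/n).

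| k | Full-MEP set | All treated |
|---|---|---|
| 0 | 0/14, 0 to 23.2% | 0/14, 0 to 23.2% |
| 1 | 0/13, 0 to 24.7% | 1/14 = 7.1%, 0.2 to 33.9% |
| 2 | 0/12, 0 to 26.5% | 2/14 = 14.3%, 1.8 to 42.8% |

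The zero-event upper limit moves little between 14 and 12 patients (23.2% to 26.5%). The harm is therefore not lost precision. It is that observed events can be left out of the summary by rule.

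**The case against.** The strongest reply is that safety itself is not compromised. Adverse events are documented, and under Organizational framework serious ones go to a safety database, the safety board, the ethics committee and the regulator. That stands. A reader might infer that anyone who drops out after a dose vanishes from the safety results, but the documents do not support this: exclusion is per experiment, applies only without a full MEP set, and touches the planned analysis, not recording or oversight.

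Four further points also stand.

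- The step from 12 to 14 is an allowance that also covers technical failures and patients never dosed. It is not a forecast that two dosed patients will be lost, and nothing documented shows that those lost would be the ones with events.
- The day-187 limit in Table 1 spans both Noonan experiments, so it is not the interval over which one set is judged.
- A patient with one session contributes no pair to a paired t-test under any set, and one common set for three Holm-adjusted time points is a legitimate choice. It would be wrong to say that the rule weakens the primary test through such patients. A mixed model or a new name for the set is optional.
- Safety is descriptive in a small phase IIa study.

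The remaining reply is that this is a condensed article, that the full protocol is a separate German document, and that ITT and PP appear in the abbreviation list, so other sets may be defined elsewhere. This does not remove the point. The article does not leave the population open; it assigns all analyses to one set. A silent SAP would inherit that rule, and an SAP with a safety set would contradict it.

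**Conclusion.** The point holds in a bounded form. As written, the rule omits dosed patients without a full MEP set from that experiment's planned safety analysis, and omits patients with paired TAP or SICI data but incomplete MEPs from those analyses. The justification conflicts with sessions 7 to 60 days apart (Experiments I and III) or about 17 to 63 days apart (Experiment II), and with the plan's own dropout allowance.

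The number affected is unknown. The range of 0 to 2 of 14 per experiment is an assumption, and the contrast of 0/12 with 2/14 is its extreme case. Both use planned numbers. Trial status reports 16 participants enrolled in total against 28 planned, so the actual sets are smaller and each excluded patient weighs more. The primary test and its stated power are not affected.

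**What to change.** 1. Restrict the full-MEP set to the primary MEP analysis.
2. Define a safety set of all patients who took at least one dose, and summarise events by the treatment received in each period.
3. Analyse TAP and SICI on all patients who have that measure under both treatments.
4. Remove the statement that data will be all present or all absent, and say which set the baseline tables describe.

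The cost is wording and a denominator that differs between tables, so each table must state its own n. No new data are needed. Recruitment has closed and the last visit has taken place, so the change belongs in the SAP and the report. The report should also state, per experiment, how many dosed patients fell outside the full-MEP set and what events they had.

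### The stated global significance level of 5% is in fact 5% per disease group; across the three experiments the error can reach 9.75%

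*Protocol article*

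**What the plan says.** All of this stands in the protocol article under Analyses and statistics, unless noted.

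- **Structure.** "The primary endpoint analyses will be performed in three separate testing procedures". Under Endpoints and endpoint rationale, the primary endpoint "for each experiment is the difference between the amplitude of the motor evoked potential (MEP") after placebo and after medication. There are therefore three primary comparisons, each at three time points.
- **Claimed overall level.** The Primary endpoint paragraph says "The global significance level will be 5"%. The Sample size paragraph says that twelve patients per disease give adequate power for every planned primary test, "with a global significance level of 5% and adjusted local significance levels using the Bonferroni-Holm procedure".
- **Allocation between experiments.** "Since experiments I and II are done on the same set of patients, the significance level for those two experiments will each be 2.5"%. Then: "The significance level of experiment III will be 5"%.
- **Within each experiment.** "The local significance level will be adjusted using the Bonferroni-Holm procedure", applied to three paired t-tests.

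No sentence makes the test of one experiment conditional on another. No sentence limits the word global to a disease group.

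**The concern.** A global level normally bounds the probability of any false rejection among all the tests it covers. Here it is attached to all primary tests, yet the levels actually assigned add up to twice that figure. The 5% is shared only between experiments I and II, and experiment III receives a second full 5%. That experiment III uses different patients makes its errors independent of those in the Noonan group. It does not take experiment III out of an error rate described as global.

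At stake is how a positive result may be described. If one of the three experiments is positive and the report says the trial controlled its error at 5% globally, that statement would be wrong by up to a factor of about two. The article's Trial status section reports early closure with 16 participants enrolled against 28 planned, so a mixed set of results is possible and the wording matters.

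**Working it through.** **Inputs (Analyses and statistics).** Levels: 0.025 (I), 0.025 (II), 0.05 (III). Experiments I and II share patients; III has its own. Power table: differences 0.520, 0.630 and 0.730 at T1, T2 and T3, common SD 0.5, n = 12 or 14, "two-sided paired samples" t-tests.

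**Step 1: were these levels really used?** I recomputed the power table with a noncentral t distribution on n − 1 degrees of freedom and noncentrality (difference / SD) × √n, taking 0.5 as the SD of the paired difference. For example, at T1 with n = 12 the noncentrality is 0.52 / 0.5 × √12 = 3.60.

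| Experiment, n | Printed (T1/T2/T3) | Recomputed |
|---|---|---|
| I and II, 12 | 82 / 89 / 94% | 82.6 / 89.4 / 94.1% |
| I and II, 14 | 89 / 95 / 97% | 89.6 / 95.0 / 97.9% |
| III, 12 | 90 / 94 / 97% | 90.6 / 94.5 / 97.6% |
| III, 14 | 94 / 97 / 99% | 94.9 / 97.7 / 99.3% |

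All twelve cells agree within one point. The full 2.5%, 2.5% and 5% are the operative levels, not a slip of typing.

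**Step 2: the error these levels give.** Assume no drug has an effect and each experiment holds its own level.

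- Noonan group (I and II): at most 0.025 + 0.025 = 0.05, whatever the dependence between the two.
- NF1 group (III): at most 0.05.
- Different patients, hence independent: 1 − (1 − 0.05)(1 − 0.05) = 0.0975.
- If all three experiments are treated as independent: 1 − 0.975² × 0.95 = 0.0969.
- Simple sum, with no independence assumption: 0.025 + 0.025 + 0.05 = 0.10.

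None of these is 0.05.

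**Step 3: allowance for correlated time points.** Holm over three correlated tests is conservative, so the attained rate lies below the ceiling. The article gives no correlation, so it is an assumption here. The global null was simulated with n = 12 and a correct Holm procedure (200,000 replicates). The experiments were combined as independent, 1 − (1 − a)²(1 − b), where a is the rate in I or II and b the rate in III.

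| Correlation | a | b | Trial-wide |
|---|---|---|---|
| 0 | 0.0253 | 0.0486 | 9.6% |
| 0.5 | 0.0231 | 0.0462 | 9.0% |
| 0.8 | 0.0193 | 0.0370 | 7.4% |
| 0.95 | 0.0143 | 0.0270 | 5.5% |

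At a correlation of 0.999 the rate falls to 3.5%, but only because Holm is then very conservative. Nothing in the plan relies on near-perfect correlation.

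**Step 4: what a true 5% over the trial would cost.** With 0.05 / 3 = 1.67% per experiment, in the same layout as the printed table, power at T1/T2/T3 is about 77 / 85 / 91% with n = 12. With n = 14 it is about 85 / 92 / 97%.

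**The case against.** The best defence is that control per disease was meant all along. The level is split between experiments I and II because they share patients, and that reason makes sense only if the family of tests is the patient group. The sample-size sentence is about patients per disease, and it sets the global level against the local levels of the time points, so global may mean no more than the level above the time points. The article describes a series of three experiments with separate testing procedures and separate analysis sets, and it states its aims by drug and disease. Whether to adjust across independent populations in a phase IIa trial is a matter of choice.

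Most of this stands. The reading is plausible and the allocation is defensible on it. What does not stand is that nothing needs correcting: the article never limits global to a disease group, and the sample-size sentence ties the level to all primary tests.

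Two stronger readings are tempting. A reader might infer that the levels must be re-split or that the sample size is wrong. The documents do not support this: the power table reproduces at the printed levels, and per-disease control is legitimate if stated. A reader might also combine this point with the table of local significance levels and infer a trial-wide error far above 9.75%. That depends on whether the first test in that table is the one with the smallest or the largest p-value, which the table does not say. It is a separate question and is not counted here.

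**Conclusion.** The contradiction is real, but it lies in the statement of error control and not in the design or the arithmetic of the power table. The design controls 5% familywise per disease group. Over all three experiments the ceiling is 9.75%, and about 7% to 9% is likely for time-point correlations of 0.5 to 0.8.

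The 9.75% assumes that each experiment holds its own level by a correctly applied Holm procedure and that the two disease groups are independent. The 7% to 9% further treats experiments I and II as independent although they share patients; using the Bonferroni sum for that pair instead changes it by less than 0.1 percentage point (9.03% and 7.42% at correlations of 0.5 and 0.8).

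Severity is moderate: the stated property should be corrected before results are reported under it, but no test or patient number has to change.

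**What to change.** In both the Sample size and the Primary endpoint paragraphs, replace the global 5% with wording such as: *5% familywise per disease group (NS: experiments I and II at 2.5% each; NF1: experiment III at 5%); trial-wide error up to 9.75%*. Add that confirmatory conclusions are drawn per disease only. This costs a sentence in each place. All levels, the printed power figures and the sample size stay as they are. The 9.75% should be quoted only once it is clear that Holm is applied correctly within each experiment.

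Only if the sponsor intends 5% over the whole trial must the levels be split over all three experiments and the power restated for each experiment whose level falls. At 1.67% each and n = 12, the printed 82 / 89 / 94% (I and II) and 90 / 94 / 97% (III) would become about 77 / 85 / 91%. That option is a choice and not a requirement.

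### The fixed 2.5%/2.5% split between Experiments I and II is valid but needlessly conservative: a fully successful experiment could pass its 2.5% to the other

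*Protocol article*

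**What the plan says.** The rule is in the Protocol article, "Analyses and statistics", paragraph on the primary endpoint.

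- The experiments are kept apart: "The primary endpoint analyses will be performed in three separate testing procedures".
- The overall level: "The global significance level will be 5" per cent.
- Lamotrigine and lovastatin in Noonan syndrome: "Since experiments I and II are done on the same set of patients, the significance level for those two experiments will each be 2.5" per cent.
- Lamotrigine in NF1: "The significance level of experiment III will be 5" per cent.
- Inside each experiment, over the three time points: "The local significance level will be adjusted using the Bonferroni-Holm procedure".

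The sample-size table gives "Local α 0.025 0.013 0.008" for Experiments I and II and "Local α 0.050 0.025 0.017" for Experiment III. The table of local significance levels that follows the primary-endpoint paragraph repeats these values. No Noonan-group test can therefore be carried out above 0.025, and no sentence lets one experiment's alpha move to the other.

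**The concern.** Holm's method rests on the idea that a rejected hypothesis no longer needs its share of alpha, so the share can be reused. The plan applies this between time points but not between the two Noonan experiments. Suppose lamotrigine is significant at all three time points. The only Noonan hypotheses left are then the three for lovastatin, yet they are still tested within 2.5%, although the plan has assigned 2.5% + 2.5% = 5% to this group. The same holds with the drugs exchanged.

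What is at stake is power for the second drug. The section on trial status reports early closure with 16 participants enrolled against 28 planned, so power is already below what was intended.

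**Working it through.** **Inputs.** From the sample-size table: differences of 0.52, 0.63 and 0.73 at T1, T2 and T3, and a common SD of 0.5, used here as the SD of the paired difference. The test is a two-sided paired t-test. Assumed, because the document does not give them: correlation of 0.5 to 0.8 between time points, independence of Experiments I and II, and 8 Noonan patients at closure (16 split equally).

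**Step 1: reproduce the plan's power.** Power is taken from the non-central t distribution with n − 1 degrees of freedom and non-centrality (difference / 0.5) × √n. The level is 0.025/k for Experiments I and II and 0.05/k for Experiment III, with k = 1, 2, 3 for T1, T2, T3. For the row "Power with 12 patients":

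| Level | Plan | Recomputed |
|---|---|---|
| 2.5% (I and II) | 82 / 89 / 94% | 82.6 / 89.0 / 94.3% |
| 5% (III) | 90 / 94 / 97% | 90.6 / 94.5 / 97.5% |

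The rows for 14 patients also agree within one point. The effects are the same in both lines, so the differences of 8.0, 5.5 and 3.2 points are what the stricter level costs. They are an upper guide to what recycling could return, because they suppose that the other experiment has already passed its alpha on.

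**Step 2: is passing alpha on valid?** Take the rule that 2.5% moves only after all three hypotheses of one experiment are rejected.

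- If each experiment contains a true null, alpha can move only after a true null has been rejected. The first false rejection therefore happens at the starting levels, with probability at most 2.5% + 2.5% = 5%.
- If only one experiment contains true nulls, it is tested by Holm at no more than 5%.

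The Noonan-group error is at most 5% either way. Everything rejected under the fixed split is still rejected, and in simulation no rejection was lost.

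**Step 3: size of the gain.** Let p be the chance that an experiment rejects all three at 2.5%, and q the same at 5%. With independent experiments and equal effects, recycling gives p + p(q − p). The gain is thus the cost q − p multiplied by the chance p that the other experiment triggers the transfer. Simulated, with both drugs at the planning effects and correlation 0.5 to 0.8:

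| | Fixed split | With recycling |
|---|---|---|
| All three time points, n=12 | 78-80% | 86-87% |
| All three time points, n=8 (assumed) | 42-48% | 49-56% |
| Any time point, n=12, correlation 0.5 | 98.1% | 99.1% |
| Any time point, n=12, correlation 0.8 | 95.7% | 97.7% |

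At n=8 the gain at any time point is about 3-5 points; with correlation 0.5 it is 82% to 86%.

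**Step 4: smaller effects.** The planning difference is healthy controls minus NF1 patients, so it amounts to full normalisation. At half that effect the transfer is triggered in only 3-17% of trials, and the gains are about 0-2.5 points.

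**Step 5: error when one drug works and the other does not.** With n=12 and correlation 0.5, Holm at 2.5% gives a false-positive rate of about 2.3% for the null drug, and Holm at 5% about twice that, 4.6%. The transfer is triggered with probability 0.78, so 0.78 × 4.6% + 0.22 × 2.3% = 4.1%; simulation gives 4.06%. Over the settings examined the rate moves from about 2% to 3-4.7%. With both drugs null it does not change.

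**The case against.** **The split is a legitimate choice.** It is conservative, its reason is given, and the planned power is at least 82% at every time point. This stands: nothing here is stated wrongly, and a reader should not infer that the plan's error control fails on this point.

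**A reader might infer that half the alpha is lost as soon as one drug succeeds.** The documents do not support that. The full 2.5% is freed only when all three time points of one experiment are rejected. A win at one or two time points releases nothing under the rule proposed here. Even a single Holm procedure over all six tests would, after one rejection, give the other drug only 3 × 0.05/5 = 0.03 instead of 0.025.

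**A reader might also take 90/94/97% against 82/89/94% as the gain.** That comparison assumes the transfer always happens. At n=12 under the planning effects it happens about 78-80% of the time, and at n=8 about 42-48%.

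**Passing alpha on is a trade-off.** When one drug works and the other does not, the fixed split has roughly half the false-positive risk. That is true. But the added risk stays within the 5% the plan already assigns to the Noonan group, so it does not argue for the fixed split.

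**The spare alpha exists only if 5% is meant per disease group.** The plan names one global 5%, while the levels add up to 2.5% + 2.5% + 5% = 10% over the three experiments. If 5% were meant for the whole trial, recycling would move further from it: with one Noonan drug effective and the other two experiments null, the overall error rises from about 7% to 8.6-9.0%. This condition stands and has to be settled first.

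**Timing.** The last patient's last visit has taken place, and the document does not say whether the data have been unblinded. Relaxing a primary threshold at this stage costs some credibility and is acceptable only while the data remain blinded.

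**Conclusion.** The point holds as a matter of efficiency. The document fully specifies a fixed split, and a rule with the same 5% limit in the Noonan group rejects everything that split rejects and sometimes more.

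The benefit lies mainly in showing an effect at all three time points: about 7-8 points at both n=12 and n=8. For detecting a drug at all, the gain is small. If the true effects are half those planned, little changes on either measure.

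These sizes rest on an SD of paired differences of 0.5, correlation of 0.5 to 0.8 between time points, independent experiments although the same patients take part in both, and an assumed 8 Noonan patients at closure. The conclusion also depends on reading 5% as a per-disease level and on Holm starting with the smallest p-value at alpha/3. The plan's table numbers the 0.025 level as test 1 and leaves that order unclear.

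**What to change.** Keep 2.5% as the starting level for each of Experiments I and II and keep Holm within each, stating that the smallest p-value is compared with alpha/3, the next with alpha/2 and the largest with alpha. State that the 5% applies per disease group. Then add, in the primary-endpoint paragraph or the SAP: if all three null hypotheses of one Noonan experiment are rejected, its 2.5% passes to the other, which is then tested by Holm at 5% (0.0167, 0.025, 0.05); this applies in either direction.

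The cost is one sentence and no new data, plus the somewhat higher false-positive risk when only one of the two drugs works. It must be fixed and dated before unblinding. If the data are already unblinded, the fixed split should stay for the primary analysis.
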